#### Step 3a: Home-based assessment (Confirmed PD only)

Within ~1 month of Step 2, participants will be asked to abstain from their dopaminergic medication overnight for 12 hours, and researchers will attend their home in the morning prior to their morning dose, to conduct the home-based testing.

*Conducted in OFF medication state*. We will collect the following details when OFF medication: MoCA and UPDRS-III.

*Conducted in OFF and ON medication states*. *OMT*: OMT will be measured using the iTremor Device in the same manner as Step 2 (see above for details). OMT testing will be conducted immediately when attending the home (OFF state, after 12hours medication withdrawal), and then again 60 minutes after the participant has taken their usual dopaminergic medications.

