Neurological disease also significantly decreases OMT frequency when compared to healthy controls. For example in PD, a study reported a mean OMT frequency of 67.68Hz (Healthy range = 70 – 130Hz [29]). In another study focusing on OMT and idiopathic PD, authors observed two groups–an ON group and OFF group [20]. These were determined using the bradykinesia subsection of the Webster Scale [32]. A score of 0 or 1 was considered ON (n = 12), and a score of 2 or 3 was considered OFF (n = 10). The healthy controls in this study had a mean OMT frequency of 81.64Hz (SD = 6.10) and both PD ON, and PD OFF, groups exhibited significantly lower OMT frequencies of 73.78Hz (SD = 5.55) and 58.88Hz (SD = 10.35) respectively; the mean frequency of the OFF group was significantly lower than that of the ON group. This preliminary evidence suggests that People with PD have reduced OMT, thus supporting the need for more robust evidence.

PD related motor symptoms tend to only be noticed when there has been a ~80% depletion of striatal dopamine and so identification of the disease using OMT as an objective measure could benefit prognosis and likely help identify subtle changes in the early stages [33]. Observing OMT through multiple recordings in patients in an ON and OFF state could yield insight to individual responsiveness to dopaminergic medication. Exploring OMT as a biomarker for PD using accessible novel technology could facilitate an objective diagnosis and monitoring of the disease and it’s progression [24]. Overall, this presented protocol aims to examine OMT as a potential marker for PD and for disease monitoring. To achieve this, the following aims are outlined:

Analytical Validation: (1) Investigate the test-retest reliability of the iTremor ONE device in measuring OMT frequency (Hz) in People with PD; (2) Investigate the feasibility of measuring OMT using a hand-held device in a real-world clinical setting. This will cover the reliability and feasibility of OMT measurement in People with PD.

Clinical Validation: (1) Compare OMT frequency in People with PD and age-matched controls, and suspected PD patients; (2) Explore relationships between OMT measurement in People with PD and other clinically relevant outcomes (e.g., UPDRS); and (3) Examine the effect on OMT of dopaminergic medication in PD. This will cover known groups validity, convergent/divergent validity and response to a known intervention in People with PD.

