**Fig 1 pone.0313452.g001:**
[figure not shown]
SPIRIT diagram, schedule of enrolment and assessments.

#### Step 3a) Home assessment 1

We will recruit 30 people with confirmed PD to participate in a home based assessment.

#### Step 3b) Home assessment 2

We will recruit 20 people with confirmed PD who participated in step 3a to participate in a second re-test home based assessment of reliability.

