*OMT assessment*: OMT will be measured using the iTremor Device (Fig 2). The participant will be asked to sit comfortably with their head resting on the chair’s headrest. If the participant wears glasses or contact lenses they will be asked to remove these for the duration of the recordings. The participant is asked to look straight ahead at a target on the wall without straining their eyes for a ~3 second period. The participant remains relaxed whilst the researcher positions the device, gently leaning on the participants cheek and brow bone. The guide light is lined up from the side of the eye with the scleral surface of the eye and the researcher cues the participant to not blink before pressing the trigger on the device. An optical beam is emitted from a diode in the device at low power with light scattered back from the eye and reflected back into the device and passed to a video imaging sensor. Three readings will be taken for each eye. If the participant blinks, the reading is just repeated. Unwanted eye movements or blinks are filtered out in raw data post-processing. A frequency will be shown on the device’s display screen in Hz. This is repeated three times for each eye independently.

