#### Step 3b: Home-based assessment 2 (Confirmed PD only)

Participants from step 3a will be invited to participate in an additional home based assessment to explore the reliability of OMT measurement in PD using the iTremor ONE device. For this, we then visit the participant at the same time as step 3a, one week later. To perform the test re-test reliability, we ask participants to take their medication at the same time as they took it for step 3a. We will collect the following details when ON medication: MoCA, UPDRS-III and OMT (60 minutes after the participant has taken their usual dopaminergic medication).

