To examine whether OMT can differentiate PD from age-matched controls, we will use an ANOVA, with group (PD vs control) as a between-subject factor. Again, to adjust for covariates (i.e. disease severity/ cognitive function), we will use analysis of covariance (ANCOVA). Receiver operating characteristic (ROC) curve analyses will also be used here to determine the relative sensitivity and specificity of OMT for differentiating People with PD and healthy controls. This provides AUC which is a metric to evaluate the classifiers output quality.

*Clinical validation aim II*. *Convergent / Divergent validity*: Pearson’s correlations will be used to detail the relationships between OMT measurement and other clinically relevant outcome measures, such as the UPDRS or MoCA.

*Clinical validation aim III*. *Known intervention response*: To examine whether OMT reduces when in the OFF-medication state in PD, we will use an ANOVA with medication-state (ON vs OFF medication) as repeated measures.

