### Clinical validation

This protocol aims to explore the ability and clinical usefulness of OMT as a potential future biomarker for PD compared to healthy controls, and suspected PD patients for diagnosis and disease monitoring. Early diagnosis would allow for improved patient care plans and the chance to trial neuroprotective therapies to slow down the development and progression of the disease. This protocol also aims to determine the clinical usefulness of OMT measurement in response to medication as a monitor of treatment plans. This understanding again, would allow for overall improved patient care and improved individualised treatments.

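### Step 3a always measures OMT OFF first and ON second, with no second OFF or undosed set, so any same-morning drift is counted as the medication effect

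*Protocol article*

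**What the plan says.** All references are to the protocol article.

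- **Order of measurement (Step 3a, home-based assessment).** "OMT testing will be conducted immediately when attending the home (OFF state, after 12hours medication withdrawal), and then again 60 minutes after the participant" (the interval runs from the usual dose). MoCA and UPDRS-III are also collected in the OFF state at this visit. No other order, undosed repeat or second OFF set is described.
- **Number.** "We will recruit 30 people with confirmed PD to participate in a home based assessment".
- **Readings in each state.** Step 3a uses the Step 2 method, under which "Three readings will be taken for each eye". That makes six readings OFF and six ON.
- **Repeat visit (Step 3b).** "We will recruit 20 people with confirmed PD who participated in step 3a to participate in a second re-test home based assessment of reliability". It takes place one week later at the same time of day: "We will collect the following details when ON medication: MoCA, UPDRS-III and OMT", with OMT again 60 minutes after medication. The two sessions are compared by ICC(2,1) and Bland-Altman limits of agreement (Statistical analysis, analytical validation aim I).
- **Analysis of the medication effect (Statistical analysis, clinical validation aim III).** "we will use an ANOVA with medication-state (ON vs OFF medication) as repeated measures".
- **What is hoped for.** The Introduction says: "Observing OMT through multiple recordings in patients in an ON and OFF state could yield insight to individual responsiveness to dopaminergic medication". The Discussion, under Clinical validation, says that the protocol "aims to determine the clinical usefulness of OMT measurement in response to medication as a monitor of treatment plans".

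**The concern.** Every participant gives the OFF value at the first measurement of the morning and the ON value at the second. Between the two come MoCA, UPDRS-III, the dose and a 60-minute wait. Medication state is thus the same variable as first versus second measurement. Three things other than the drug can fall on the ON value: getting used to a device resting on the cheek and brow while trying not to blink, time since waking, and tiredness after testing.

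Clinical validation aim III, the response to a known intervention, rests on this one contrast. A same-direction drift would inflate the apparent effect or create one, and an opposite drift would hide a real one. Because the two variables coincide completely, no later analysis can separate them. The problem has to be met at data collection.

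**Working it through.** The protocol states no sample size or power figure for this comparison, so there is none to reproduce. The check has two parts.

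**1. Do the existing repeats identify the drift?**

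| Data collected | What it estimates | What it leaves open |
|---|---|---|
| Three readings per eye within each state | Short-term reading noise, OFF and ON | Change between two sets taken at different times of the same morning |
| Step 3b ON versus Step 3a ON, 20 people, one week apart | ON repeatability between visits, with limits of agreement | OFF repeatability between sets; any drift common to both mornings, which cancels in this comparison |
| Reported absence of a time-of-testing effect (Introduction) | Clock time, in earlier work | First versus second recording with this device |

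None of the three gives the change expected over the morning without a dose.

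**2. How much could a drift matter?**

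*Inputs from the document:* 30 participants; two-sided 5% level; ON SD 5.55 Hz and OFF SD 10.35 Hz from the cited PD study (Introduction). These come from separate groups of 12 and 10 people.

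*Assumptions:* correlation r between a person's OFF and ON values; drift d; no drug effect.

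SD of paired differences = √(5.55² + 10.35² − 2r × 5.55 × 10.35)

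- r = 0.3: 10.2 Hz
- r = 0.5: 9.0 Hz
- r = 0.7: 7.6 Hz

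A repeated-measures ANOVA with two levels is equivalent to a paired t-test. Its rejection probability comes from the noncentral t distribution with 29 degrees of freedom and noncentrality d / (SD/√30). For d = 3 and SD = 9 the noncentrality is 3 / (9/5.477) = 1.83, which gives 42%.

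| Assumed drift | r = 0.3 (SD 10.2) | r = 0.5 (SD 9.0) | r = 0.7 (SD 7.6) |
|---|---|---|---|
| 2 Hz | 18% | 22% | 29% |
| 3 Hz | about 35% | 42% | 55% |
| 4 Hz | 55% | 65% | 80% |

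The nominal figure is 5% throughout.

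*Scale:* the cited study's ON minus OFF difference is 73.78 − 58.88 = 14.90 Hz. A drift of 2 to 4 Hz is 13% to 27% of that (2/14.9 and 4/14.9).

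*Individual change:* suppose the cited SDs hold and the ICC is the same in both states. The 95% noise band for one person's ON minus OFF change is then 1.96 × √(1 − ICC) × √(5.55² + 10.35²). This is ±16.3 Hz at ICC 0.50, ±11.5 Hz at 0.75 and ±7.3 Hz at 0.90. A 14.9 Hz change in one person would exceed noise at an ICC of 0.75 or above, but not at 0.50.

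**The case against.** The drift is hypothetical: the document reports none. The Introduction says that time of testing has not been found to affect OMT, and the Equipment section says that the method works regardless of other eye movements and head movements. Participants who attended the laboratory visit have already had the device used on them. OFF on arrival followed by ON 60 minutes after medication is also the sequence of an earlier saccade study that the Introduction describes, and home testing was chosen to limit time OFF. The study is an exploratory pilot.

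Much of this stands as a limit on size. It makes a large drift less likely and shows that the sequence is conventional. It does not remove the confounding. Clock time is not the same as first versus second recording, the Introduction itself lists caffeine as affecting OMT, and home-only participation is allowed, so prior experience of the device is not assured.

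Two stronger readings are tempting. A reader might infer that nothing is repeated within a state. That is wrong: there are six readings in each state and an ON repeat in 20 people. A reader might also infer that individual responsiveness cannot be told from noise. The document does not support that either. The Step 3b limits of agreement supply a noise band, and whether a given change exceeds it depends on the reliability that Step 3b is designed to measure. Individual responsiveness is in any case a hoped-for insight; the numbered aim and its test are at group level. What remains is narrower. OFF repeatability between sets is not estimated, and because the cited OFF SD is nearly twice the ON SD, a band from ON values alone may be too narrow for an OFF-to-ON change.

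**Conclusion.** The concern holds for the group contrast. Order and medication state are fully confounded in Step 3a, and neither the within-session readings nor Step 3b measures undosed change over the same morning. At an SD of differences of 9 Hz, an assumed drift of 2, 3 or 4 Hz with no drug effect would be reported as a medication effect in about 22%, 42% or 65% of studies. Across correlations of 0.3 to 0.7 the range is 18% to 80%.

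These figures rest on assumed drifts, an assumed correlation, and SDs from two small separate groups. They show sensitivity and do not predict what will happen. A reader might infer that drift could explain away a result as large as the cited 14.9 Hz. A drift of a few Hz could not do that by itself; it would bias the estimate and the test. This is a worthwhile and inexpensive improvement to the design, and the comparison remains usable without it if the limit is stated.

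**What to change.** 1. At Step 3a, take a second set of OFF OMT readings after MoCA and UPDRS-III, immediately before the participant's usual dose. Leave the medication timing rules as they are.
2. Use this pre-dose set as the OFF value in the aim III ANOVA. This takes first-recording and arrival-to-dose effects out of the contrast.
3. Report the arrival-to-pre-dose change with its confidence interval, as a partial estimate of undosed drift.
4. Describe the result as an OFF-to-ON change, and state that drift over the 60 minutes after the dose remains unmeasured and that ON still always comes last.
5. Judge any individual change against the Step 3b limits of agreement together with the spread of the two OFF sets. That spread contains drift as well as noise, so it should not be used alone.

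Cost: six more readings of about three seconds each in a visit that already takes place, a few more minutes before the dose, and slightly more data handling.

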*Contrast sensitivity—LogCS*. This is measured using the Mars CS sheets. These sheets consist of 48 Latin letters of uniform height, and the contrast from the white background decreases with each letter. The participant is seated 50 centimetres (cm) from the sheet and again reads from left to right, starting at the top left. Errors are recorded by the investigator and the test is terminated when two consecutive errors are made. LogCS is calculated using the following formula: (value of final correct letter before stopping)–(number of errors prior to stopping x 0.04). Again, answers are recorded for binocular vision then for left, and right eyes independently using an occluder.

*Motor assessment*: To assess disease severity and motor symptoms in People with PD, the Movement Disorder Society Unified Parkinson’s disease Rating scale part III (UPDRS-III) is used [45]. The motor assessments should take around 30 minutes. The UPDRS will be conducted first before setting up the sensors for the balance and gait assessments. People with PD will be categorised based on their disease severity using the Hoehn and Yahr scale (H&Y) [46]. This is a widely used clinical scale for defining motor symptoms in PD, which is a part of the UPDRS-III. It consists of five stages–stage I, unilateral symptoms with no functional disability, to stage V, complete disability and patient is bedbound. This scale is easily applicable and widely used to assess PD. There will also be a short self-report questionnaire on freezing of gait, using the new Freezing of Gait Questionnaire (nFOGQ) [47]. In addition, the Falls Efficacy Scale–International (FES-I) [48], a self-report evaluation to assess fear of falling will be completed.

*Balance*. Participants will stand for several periods of up to 2 minutes under different conditions (i.e., eyes open, eyes closed, and on a foam block with eyes open, and closed) with balance measured via mobile inertial measurement units (APDM, USA). These sensors are located at the wrists, feet, chest, and lower back to measure postural sway.

*Gait*. Participants will walk back and forth over a marked out 10m distance for several periods of up to 2 minutes under different conditions (i.e., normal walking and walking while repeating numbers) with gait measured via mobile inertial measurement units (APDM, USA). Turns are included in this walking sequence. These sensors are located at the wrists, feet, chest, and lower back.

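### At the Step 3a home visit the OFF OMT value is displayed before the OFF UPDRS-III is scored, so the convergent-validity correlation from that visit is open to rater bias of unknown size

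*Protocol article*

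**What the plan says.** Under Step 3a, "researchers will attend their home in the morning prior to their morning dose, to conduct the home-based testing". Two statements there concern the OFF state. The first is "We will collect the following details when OFF medication: MoCA and UPDRS-III". The second is that "OMT testing will be conducted immediately when attending the home", with a repeat reading 60 minutes after the usual medication.

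The home reading uses the laboratory procedure: "OMT will be measured using the iTremor Device in the same manner as Step 2". The OMT assessment paragraph of Step 2 describes three readings per eye and adds "A frequency will be shown on the device’s display screen in Hz".

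Under Statistical analysis, clinical validation aim II uses Pearson's correlations for "relationships between OMT measurement and other clinically relevant outcome measures, such as the UPDRS or MoCA". The article does not say who operates the device, who scores UPDRS-III, or whether the rater is kept from the OMT value.

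**The concern.** Convergent validity asks whether a new measure agrees with an established one that was obtained independently of it. UPDRS-III is scored by an observer and leaves room for judgement. If the observer already knows the OMT result, part of the agreement may come from that knowledge.

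The direction of any drift is predictable. The Introduction reports mean OMT of 81.64 Hz in controls, 73.78 Hz in PD ON and 58.88 Hz in PD OFF. A rater who knows this background could take a low reading as a sign of worse disease and score accordingly. The bias would lie in UPDRS-III, not in the OMT frequency, and it could not be separated from true association at the analysis stage.

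The Step 3a OFF pair matters because it has 30 planned participants and a stated medication state. Step 3b has 20 participants, and the Step 2 text does not state the medication state of its UPDRS-III and OMT pair.

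**Working it through.** **Order of events at Step 3a**

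1. OFF OMT is taken immediately on arrival.
2. The Hz value appears on the device. With three readings for each of two eyes, about 3 × 2 = 6 values are shown.
3. OFF UPDRS-III must be done before the dose, because it is collected OFF. It therefore falls after step 1. MoCA has the same timing.
4. The usual medication is taken, and OMT is repeated 60 minutes later.

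So the stated order puts the visible OMT result before the observer-rated comparator.

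**Illustration of sensitivity (the document gives no figure to reproduce)**

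Inputs from the document: n = 30 (Step 3a) and two-sided 5% tests (Statistical analysis). Assumed inputs: the true correlation, of size ρ in the hypothesised negative direction, and a rater shift of b SD of UPDRS-III per SD of lower OMT.

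Let Z be standardised OMT and U the standardised unbiased UPDRS-III, with correlation −ρ. The recorded score is U − bZ. Its covariance with Z is −(ρ + b) and its variance is 1 + b² + 2bρ, so

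|r observed| = (ρ + b) / √(1 + b² + 2bρ).

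- ρ = 0.30, b = 0.1: 0.40 / √1.07 = 0.387
- ρ = 0.30, b = 0.2: 0.50 / √1.16 = 0.464
- ρ = 0, b = 0.2: 0.20 / √1.04 = 0.196

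At n = 30 the critical |r| is 0.361. The chance of p < 0.05 comes from the Fisher approximation: with m = atanh(|r observed|) × √27, it is Φ(m − 1.96) + Φ(−m − 1.96).

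| True size ρ | Assumed b | Expected size of r | Chance of p < 0.05 |
|---|---|---|---|
| 0 | 0 | 0 | 5% |
| 0 | 0.1 | 0.10 | 8% |
| 0 | 0.2 | 0.20 | 18% |
| 0 | 0.3 | 0.29 | 34% |
| 0.30 | 0 | 0.30 | 36% |
| 0.30 | 0.1 | 0.39 | 56% |
| 0.30 | 0.2 | 0.46 | 74% |
| 0.30 | 0.3 | 0.53 | 87% |

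The table shows only that modest rater shifts matter at this sample size. It says nothing about how large b is, or whether it differs from zero.

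**The case against.** **Roles are not stated.** More than one researcher attends, and a condensed article may leave rating and masking to the full protocol. This stands: the documents do not show that the rater will know the value. They do state an order under which the rater can, with no safeguard mentioned. If the full protocol has one, citing it closes the point.

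**The order could be read differently.** The Step 3a text lists MoCA and UPDRS-III before OMT. Listing order, however, is not testing order, and OMT is the only one of these assessments given an explicit time on arrival.

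**The source of the correlation is not named.** This also stands. Aim II could use Step 2, which collects both measures in 30 people with confirmed PD. A reader might infer that the laboratory visit is safe because "The UPDRS will be conducted first before setting up the sensors for the balance and gait assessments". That sentence places the UPDRS before the sensors only; its order relative to OMT is not fixed. The laboratory visit therefore cannot serve as a model of the protected order.

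**Re-ordering is incomplete.** Step 3a follows Step 2 within about a month, so for participants who attended both, a laboratory OMT value may already be known. Re-ordering removes same-visit knowledge only.

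**Re-ordering could move the bias to the primary outcome.** The OMT operator might then know the UPDRS-III score and decides when a blink requires a repeat reading. This is a small concern, because the device's algorithm produces the frequency.

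**The magnitude has no anchor.** This is correct. The value of b is assumed, the model takes the shift as linear in the analysed OMT value, and aim II is exploratory in a pilot without a formal sample size calculation.

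**Conclusion.** The point holds as a design weakness at Step 3a. The stated order lets a displayed OMT result precede the observer-rated OFF UPDRS-III, and the pair is available for the aim II correlation. Any resulting bias would favour the hypothesis.

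Its size is unknown. It depends on whether the rater learns the value, how far that moves the score, and whether aim II uses this visit; the document settles none of these. The figures above are conditional on an assumed b and are not estimates for this study.

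Two stronger readings are not supported. The first is that the correlation will be inflated: the text supports only that it can be. The second is that Step 3b has the same fault. The Step 3b text sets no order that puts OMT before UPDRS-III, and it times OMT at 60 minutes after medication to match the Step 3a ON reading for reliability. Requiring UPDRS-III and MoCA first there could conflict with that timing.

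**What to change.** At Step 3a only, state that the OFF UPDRS-III is scored and locked before the OFF OMT reading, with both still completed before the usual medication is taken. If OMT needs to come first, use one of two alternatives: have UPDRS-III scored by an attending researcher who has not seen the display, or keep the Hz value out of the rater's view until the score is recorded. Also name the visit and medication state that supply the aim II correlation.

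Re-ordering needs no extra staff, visit or test, because the same OFF assessments are already planned. Its cost is that the OFF OMT reading comes later in the visit and its operator may know the UPDRS-III score. The alternatives keep the reading on arrival, but need either two people with separate roles or control of the display. Values from Step 2 may still be known under re-ordering, and the report should say so. Leave the Step 3b timing as it is.
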